**Table 4. Simulation results: difference between investigational and control group is 0 points on mJOA scale**

| Normal Superiority Trials: Two-Sample Test - Difference of Means (Enhanced Simulation) |               |                                                                                     |           |     |        |     |                  |                                                                                      |                            |                |                |                   |       |        |
|----------------------------------------------------------------------------------------|---------------|-------------------------------------------------------------------------------------|-----------|-----|--------|-----|------------------|--------------------------------------------------------------------------------------|----------------------------|----------------|----------------|-------------------|-------|--------|
| Plan Details                                                                           |               | Simulation Boundaries                                                               |           |     |        |     |                  | Latest Simulated Test Stat.                                                          | Overall Simulation Results |                |                |                   |       |        |
| 1-Sided or 2-Sided Test                                                                | 1-Sided       | Look #                                                                              | Boundary  |     |        |     | Avg. Information |                                                                                      | Avg. Sample Size           | # Rejecting H0 | # Rejecting H1 | Total Simulations |       |        |
| Significance Level ( $\alpha$ )                                                        | 0.025         |                                                                                     | Samp Size | H0- | H0+    | H1- |                  |                                                                                      |                            |                |                | H1+               | Count | %      |
| Power (1 - $\beta$ )                                                                   | 0.8           | 1                                                                                   | 175.26    |     | 2.5469 |     | 0.9365           | -0.5658                                                                              | 6.68                       | 175.00         | 70             | 8250              | 8320  | 83.20% |
| Assigned Fraction (Treatment)                                                          | 0.5           | 2                                                                                   | 269.64    |     | 1.9896 |     | 1.9896           |                                                                                      | 10.33                      | 270.00         | 166            | 1514              | 1680  | 16.80% |
| Planned Number of Looks                                                                | 2             | 3                                                                                   |           |     |        |     |                  |                                                                                      |                            |                |                |                   |       |        |
| Spacing of Looks                                                                       | Unequal       | 4                                                                                   |           |     |        |     |                  |                                                                                      |                            |                |                |                   |       |        |
| Hypothesis to be Rejected                                                              | H0 or H1 (NB) | 5                                                                                   |           |     |        |     |                  |                                                                                      |                            |                |                |                   |       |        |
| Boundary Family                                                                        | SpF (Pub)     | 6                                                                                   |           |     |        |     |                  |                                                                                      |                            |                |                |                   |       |        |
| Boundary to Reject H0                                                                  | LD (OF)       | 7                                                                                   |           |     |        |     |                  |                                                                                      |                            |                |                |                   |       |        |
| Boundary to Reject H1                                                                  | Gm (-2)       | 8                                                                                   |           |     |        |     |                  |                                                                                      |                            |                |                |                   |       |        |
| Difference of Means ( $\delta_1$ )                                                     | 0.9           | 9                                                                                   |           |     |        |     |                  |                                                                                      |                            |                |                |                   |       |        |
| Standard Deviation ( $\sigma$ )                                                        | 2.57          | 10                                                                                  |           |     |        |     |                  |                                                                                      |                            |                |                |                   |       |        |
| Maximum Sample Size                                                                    | 270           | 11                                                                                  |           |     |        |     |                  |                                                                                      |                            |                |                |                   |       |        |
|                                                                                        |               | 12                                                                                  |           |     |        |     |                  |                                                                                      |                            |                |                |                   |       |        |
|                                                                                        |               |                                                                                     |           |     |        |     |                  | Total                                                                                | 7.29                       | 190.96         | 236            | 9764              | 10000 |        |
| Design Outputs                                                                         |               |                                                                                     |           |     |        |     |                  | %                                                                                    |                            |                | 2.36%          | 97.64%            |       |        |
| Max. Sample Size (Nmax)                                                                | 270           |                                                                                     |           |     |        |     |                  |                                                                                      |                            |                |                |                   |       |        |
| Max. Information (Imax)                                                                | 10.2060       |                                                                                     |           |     |        |     |                  |                                                                                      |                            |                |                |                   |       |        |
| Simulation Parameters                                                                  |               |                                                                                     |           |     |        |     |                  |                                                                                      |                            |                |                |                   |       |        |
| Simulation Scale                                                                       | Sample Size   |                                                                                     |           |     |        |     |                  |                                                                                      |                            |                |                |                   |       |        |
| Difference of Means                                                                    | 0             |                                                                                     |           |     |        |     |                  |                                                                                      |                            |                |                |                   |       |        |
| Standard Deviation                                                                     | 2.57          |                                                                                     |           |     |        |     |                  |                                                                                      |                            |                |                |                   |       |        |
| Number of Trials                                                                       | 10000         |                                                                                     |           |     |        |     |                  |                                                                                      |                            |                |                |                   |       |        |
| Refresh Every 'n' Trials, n =                                                          | 1000          |                                                                                     |           |     |        |     |                  |                                                                                      |                            |                |                |                   |       |        |
| Simulation Starting Seed                                                               | Clock         |                                                                                     |           |     |        |     |                  |                                                                                      |                            |                |                |                   |       |        |
| 
Run
 
Single Step
 
Reset
 
Stop
                 |               |                                                                                     |           |     |        |     |                  |                                                                                      |                            |                |                |                   |       |        |
| Trial # = 10000
Simulation Seed = 37669
Elapsed Time = 0:00:11                   |               |                                                                                     |           |     |        |     |                  |                                                                                      |                            |                |                |                   |       |        |
|                                                                                        |               | [figure not shown] |           |     |        |     |                  | [figure not shown] |                            |                |                |                   |       |        |

[figure not shown][figure not shown]

Efficacy of Riluzole in Patients with Cervical Spondylotic Myelopathy Undergoing Surgical Treatment. A Multi-Center Double Blind Randomized Controlled Study.

**Table 5. Simulation results: difference between investigational and control group is 0.9 absolute points in mJOA**

[figure not shown]

## 5.9 Adaptive Design and Sample Size Re-estimate

---

The current sample size estimate is based on numerous assumptions. The main assumption affecting the sample size is that of the true effect size and the standard deviation for the difference in the mJOA. These assumptions will be verified during the study and sample size readjustment will be performed if needed, using the adaptive techniques. The sample size readjustment will be performed after the first interim analysis of the data, currently planned at 65% data available at 180 days. The details of the adaptive change will be described in a separate Statistical Analysis Plan (SAP).

## 5.10 Analysis Populations

---

For definitions of subjects' status in the study see Section 4.6 Subjects Completion and Disposition.

### 5.10.1 Intention-to-Treat

---

Consenting patients who qualify and are randomized to a study arm (i.e. enrolled subjects) will be included in the Intent-To-Treat (ITT) analytic sample primary analysis population, regardless of the actual treatment received. Screen failures will be recorded on a screening eCRF and will not be included in the ITT group. Values for the patients who do not have the 6-month end point will be imputed to create complete ITT population.

### 5.10.2 Modified Intention-to-Treat

---

The modified Intent-To-Treat (mITT) population is defined as all consenting patients who receive study-directed treatment and have any follow-up. The mITT population will be used for safety analyses.

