### 3.3 Study Scope and Duration

---

This is a multi-center, prospective, double-blinded, randomized placebo-controlled clinical trial to evaluate if sodium-glutamate antagonist riluzole in a dose of 50mg BID 14 days before the surgery and continuing for 28 days after the surgery is superior to placebo in patients with moderate and severe cervical spondylotic myelopathy undergoing surgical decompression.

The study will involve up to 16 investigational sites and enroll 270 evaluable subjects. A randomization ratio of one riluzole subject to one placebo control subject (1:1) will be utilized. The sample size may change during the interim analysis due to adaptive statistical design.

Patients scheduled for elective surgical decompression due to cervical spondylotic myelopathy will be screened for inclusion in the study. If the patient meets all of the eligibility criteria, he/she will be enrolled and randomized to either the riluzole or placebo controlled group. The randomization will occur 14-17 days prior to surgery. Subjects will begin receiving study medications 14 days prior to the planned surgery date and continue receiving it for 28 days following the surgery. The riluzole group will receive riluzole in a dose of 50 mg every 12 hours. The control group will receive placebo capsules that are the same color, size, taste and

Efficacy of Riluzole in Patients with Cervical Spondylotic Myelopathy Undergoing Surgical Treatment. A Randomized, Double-Blind, Placebo-Controlled, Multi-Center Study

consistency as riluzole capsules but will not have the active ingredient. Subjects, investigators, and study research personnel will be blinded to the randomization code. The study Contract Research Organization (CRO) will maintain randomization and blinding. Treatment allocation will be un-blinded for the purpose of interim analysis. The results of the interim analysis and the un-blinded data will not be shared with investigators, subjects or those involved in the execution of the study.

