#### *4.5.2.5 Visit4: Procedure*

---

- Record operative data into source worksheets
- Obtain and record intra-operative and immediate postoperative AE/SAE
- Check source worksheets for completeness
- Verify data and enter into eCRF within 14 calendar days of collection

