##### *4.5.2.7 Visit 6: 35 days $\pm$ 5 days*

---

This is the first scheduled follow-up visit. The visit should occur at earliest 30 days from the date of surgery to allow subject to complete the 28 days of post-surgical treatment. The following activities should be performed during the visit.

- Subject returns bottle #2 with any remaining medication along with the Subject's Medication Compliance Diary. The remaining medication will be compared to the Subject's Medication Compliance Diary.
- Obtain and record concomitant therapy
- Obtain and record AE/SAE
- Obtain and record vitals
- Investigator performs and records:
  - ASIA (complete)
  - mJOA
  - Nurick
  - Grip Strength
- Obtain blood sample and order clinical lab tests
- Subject completes questionnaires for:
  - Health behavior
  - NDI
  - Pain NRS
  - EQ-5D
  - SF-36v2™
  - Bazaz
- Record study medication compliance in Medication Compliance CRF
- Log the subject's drug accountability information into the Site Drug Accountability Log
- Schedule next study visit (180 days post-surgery)
- Check Source Worksheets for completeness
- Verify data and enter into eCRF within 14 calendar days of collection

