### 5.10.5 Primary analysis population

---

Primary efficacy analysis will be performed on ITT population. Primary safety analysis will be performed on mITT population.

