#### 7.1.1 Adverse Event

---

An AE is any unfavorable and unintended sign (including an abnormal laboratory finding), symptom, or disease temporally associated with the use of an investigational product, whether or not it is related to the investigational product and/or any unfavorable clinical event which impacts, or has the potential to impact, the health and/or safety of a clinical study participant. Events may be: complications; observations; change in subject condition; or, (un)related death. An AE may occur at any time the subject is participating in the study and is not limited to the period of exposure to a study procedure or exposure to the study drug.

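### The safety population requires follow-up after treatment, so dosed subjects who die or are lost early can be left out of the adverse-event rates

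*Protocol*

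**What the plan says.** Section 5.10.2 defines the mITT population as "all consenting patients who receive study-directed treatment and have any follow-up" and adds: "The mITT population will be used for safety analyses". Section 5.10.5 confirms it: "Primary safety analysis will be performed on mITT population". The other populations in section 5.10 are ITT, per-protocol and completed subjects. None of them is a set of all treated subjects for safety.

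Neither section 5.10 nor section 4.6, to which it refers for subject status, says what counts as any follow-up. The nearest guidance is in the visit schedule. Section 4.5.2 counts all follow-up windows from the day of surgery. Section 4.5.2.7 says of the Day 35 visit: "This is the first scheduled follow-up visit". It adds: "The visit should occur at earliest 30 days from the date of surgery".

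Exposure starts well before that. Section 3.3 states: "Subjects will begin receiving study medications 14 days prior to the planned surgery date". Adverse-event recording also starts earlier. Table 1 marks it at admission, procedure, pre-discharge and unscheduled visits as well as at the later visits.

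**The concern.** A safety population should be fixed by exposure. Here membership also depends on something that happens after exposure, and a serious adverse event can stop it from happening. A peri-operative death is the plainest case, and section 6.1 lists death, stroke and cardiopulmonary events among the anticipated events.

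Section 4.1.4 promises the incidence of adverse events by body system and preferred term. If subjects with early serious events can fall outside both numerator and denominator, that incidence no longer describes everyone exposed. The comparison between arms is also distorted if exclusions differ by arm. Because the qualifying term is undefined, the choice between a wide and a narrow reading could be made after the data are seen.

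**Working it through.** The plan gives no figure on this point to reproduce, so the check sets the population rule against the visit schedule and then illustrates the size.

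**Timing, if follow-up starts at Day 35**

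- First dose: 14 days before surgery (section 3.3).
- Day 35 visit: window of ±5 days, so 30 to 40 days after surgery (section 4.5.2.7).
- First dose to first scheduled follow-up visit: 14 + 30 = 44 days to 14 + 40 = 54 days.
- Last dose: day 28 after surgery (section 4.5.2.6), which is before day 30.

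On this reading, the whole dosing course and the operation come before a subject can qualify for the safety population.

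**Recording over the same period**

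- Section 7.1.1: "An AE may occur at any time the subject is participating in the study".
- Section 4.5.2.4: adverse events are checked and recorded at admission.
- Section 4.5.2.5: "Obtain and record intra-operative and immediate postoperative AE/SAE".
- Sections 4.5.2.6 and 4.5.2.10: they are recorded again before discharge and at unscheduled visits.

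The protocol therefore collects events in subjects whom its safety population may leave out.

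**The two readings**

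| Meaning of any follow-up | Who is left out |
|---|---|
| A visit in the post-surgical schedule, from Day 35 | Dosed subjects who die, are withdrawn without further visits or are lost before Day 35, including those with recorded events |
| Any contact after the first dose | Only dosed subjects never seen again, who mostly have no recorded events |

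**Size (illustration)**

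Section 5.7 plans 300 enrolled at 1:1, so 300 / 2 = 150 per arm. One subject is 1/150 = 0.67 percentage points. The protocol gives no rate of early loss, so the event count and the number excluded below are assumptions. Take 5 subjects with an event in an arm of 150 and exclude k of them, giving a rate of (5 − k)/(150 − k):

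- k = 0: 5/150 = 3.3%
- k = 1: 4/149 = 2.7%
- k = 2: 3/148 = 2.0%
- k = 3: 2/147 = 1.4%

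If the 3 excluded subjects had no event, the rate would instead be 5/147 = 3.4%. The bias can run either way, but it is much larger when the excluded subjects are those with events.

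**The case against.** The strongest reply is that any follow-up is wider than the first scheduled follow-up visit, and that section 5.10.2 does not refer to Day 35. If admission, surgery, pre-discharge or unscheduled contacts count, nearly every exposed subject with a recorded event is in the set. This stands as a possible reading, and under it the loss is small. It does not remove the condition or settle which reading applies.

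Some stronger conclusions are tempting, and the protocol does not support them:

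- **That subjects who stop the drug for an adverse event drop out of the safety analysis.** Section 4.5.4.5 keeps non-compliant subjects in the study with the same procedures. Section 4.6.3 provides for a safety evaluation within 30 days of the last dose after early withdrawal. These subjects are not the main concern. Those provisions do not help subjects who die or are lost, and section 4.6.3 does not say that its evaluation counts as follow-up.
- **That the events disappear altogether.** Section 4.1.4 has every adverse event listed. A listing gives no rate and no comparison between arms, so what is at risk is the incidence summaries.
- **That riluzole's rates are certainly understated.** Excluding lost subjects who have no recorded event raises a rate, and the protocol has no data on who would be lost.
- **That the five discontinuations for raised liver enzymes in section 3.2 measure the loss.** They come from a trial in Huntington's disease that the reference list describes as lasting 3 years. Their arm is not stated, and stopping a drug is not loss of follow-up.

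It is also fair to say that an all-dosed set adds subjects with no post-dose data to the denominator and so dilutes rates slightly. Reporting their number by arm answers this.

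Finally, the separate SAP could define the term. But the follow-up condition is a rule that the protocol itself states, so this is more than a detail left for later.

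**Conclusion.** The point holds as a should-fix. Sections 5.10.2 and 5.10.5 make the primary safety population depend on a post-treatment condition that is undefined and that the outcome can prevent. How many subjects this removes depends on the reading: potentially all early deaths and losses if follow-up starts at Day 35, and few if any post-dose contact counts. The text leans towards the first through its usage in sections 4.5.2 and 4.5.2.7 but does not settle it.

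The size cannot be estimated from the protocol. The figures of 0.67 percentage points per subject and of 3.3% falling to between 2.7% and 1.4% rest on 150 treated per arm and on assumed event and exclusion counts. The direction of bias is likewise not established. The primary efficacy analysis uses the ITT population, so it is unaffected, as are sample size and power.

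**What to change.** In section 5.10.2, define a safety population of all randomised subjects who took at least one dose of study drug, analysed by the drug actually received, with no follow-up condition. In section 5.10.5, name it as the population for the primary safety analysis and use it for all safety tables. Count subjects with no post-dose contact in the denominator and report their number by arm. The one-dose rule also avoids any argument over what counts as study-directed treatment.

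The cost is a few sentences in two sections. No new data are needed, because adverse events are already recorded from admission onward and at unscheduled visits.
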